***Table 1***

***Preparing for Life* (*PFL*) Survey Content for All Waves of Data Collection**

**Parent/Family Survey Content**

| **Category** | **Measure/Information Obtained** | **BL** | **3** | **6** | **12** | **18** | **24** | **36** | **48** |
| --- | --- | --- | --- | --- | --- | --- | --- | --- | --- |
|  | Father Questionnaire Distributed | X |  | X |  |  |  |  |  |
| **Interview Details** | RA Initials |  |  |  | X | X | X | X | X |
| ID number | X | X | X | X | X | X | X | X |
| Date of Interview | X | X | X | X | X | X | X | X |
| Child’s Name (note that this is not permanently recorded in datafile) |  |  | X | X | X | X | X | X |
| Multiple Birth |  |  | X | X | X | X | X | X |
| Location of Interview |  |  | X | X | X | X | X | X |
| Survey Method |  |  |  | X | X | X | X | X |
| Child Present |  |  |  |  |  |  | X | X |
| **Demographic/**  **Household Information** | Maternal Age | X |  |  |  |  |  |  |  |
| Maternal Ethnic Group | X |  |  |  |  |  |  |  |
| Maternal Age at Birth of her First Child | X |  |  |  |  |  |  |  |
| Indicator for whether Mother was in Special/Remedial Education | X |  |  |  |  |  |  |  |
| Maternal Grandmother Age & Education | X |  |  |  |  |  |  |  |
| Maternal Grandfather Age & Education | X |  |  |  |  |  |  |  |
| Father’s Age | X |  |  |  |  |  |  |  |
| Indicator If Father was in Special/Remedial Education | X |  |  |  |  |  |  |  |
| Paternal Grandmother Age & Education | X |  |  |  |  |  |  |  |
| Paternal Grandfather Age & Education | X |  |  |  |  |  |  |  |
| Household Composition | X |  | X | X | X | X | X | X |
| Number of Mother’s Biological Children | X |  | X |  |  |  |  |  |
| Mother’s Relationship/Marital Status | X |  | X | X | X | X | X | X |
| Indicator if Partner is Biological Father |  |  | X | X | X | X | X | X |
| Maternal Highest Education Level | X |  | X |  |  |  |  |  |
| Age Mother Left Full-time Education | X |  | X |  |  |  |  |  |
| Mother’s Intention to Remain in School (if still in full-time education) | X |  | X |  |  |  |  |  |
| Maternal Education: Continuation of Education/Additional Courses Taken |  |  |  |  |  | X | X | X |
| Maternal Literacy Problems (in daily life) | X |  |  |  |  |  |  |  |
| Maternal Maths Problems (in daily life) | X |  |  |  |  |  |  |  |
| **Category** | **Measure/Information Obtained** | **BL** | **3** | **6** | **12** | **18** | **24** | **36** | **48** |
|  | Maternal Home Ownership Status | X |  | X |  |  |  | X |  |
| Mother’s Relationship with and the Involvement of the Biological Father | X |  | X | X | X |  |  |  |
| Father’s Highest Education Level | X |  | X |  |  |  |  |  |
| Age Mother’s Partner Left Full-time Education | X |  | X |  |  |  |  |  |
| **Employment/ Income Information** | Maternal Grandfather’s Main Occupation | X |  |  |  |  |  |  |  |
| Maternal Grandmother’s Main Occupation | X |  |  |  |  |  |  |  |
| Mother’s Maternity Leave |  |  | X | X |  |  |  |  |
| Mother’s Work Status | X |  | X | X | X | X | X | X |
| Mother’s Occupation | X |  | X | X | X | X | X | X |
| Mother’s Work Hours | X |  | X | X | X | X | X | X |
| Mother’s Wage | X |  | X | X | X | X | X | X |
| Maternal Job Stability |  |  |  | X | X | X | X | X |
| Mother’s Unemployment Info (if applicable) | X |  | X | X | X | X | X | X |
| Indicator for Social Welfare Payments to Household | X |  | X | X |  |  |  |  |
| Indicator for Social Welfare Payments to Household – Detailed |  |  |  |  | X | X | X | X |
| Household Weekly Income | X |  | X | X | X | X | X | X |
| Family Finances |  |  |  |  |  |  | X | X |
| Perception oF Financial Difficulty/Economic Perceptions | X |  | X | X | X | X | X | X |
| Mother’s Saving Habits | X |  | X | X | X | X | X | X |
| Partner’s Work Status | X |  | X | X | X | X | X | X |
| Partner’s Occupation | X |  | X | X | X | X | X | X |
| Partner’s Work Hours | X |  | X | X | X | X | X | X |
| Partner’s Wage | X |  | X | X | X | X | X | X |
| Partner’s Job Stability |  |  |  | X | X | X | X | X |
| Father’s Unemployment Info (if applicable) | X |  | X | X | X | X | X | X |
| **Pregnancy** | Week of Pregnancy | X |  |  |  |  |  |  |  |
| Child Due Date | X |  |  |  |  |  |  |  |
| Maternity Hospital Mother Attending | X |  |  |  |  |  |  |  |
| Week Pregnancy Confirmed | X |  |  |  |  |  |  |  |
| Week of First Antenatal Visit | X |  |  |  |  |  |  |  |
| Indicator of Mother’s Intention to take Antenatal Classes | X |  |  |  |  |  |  |  |
| Indicator of Whether Pregnancy was Planned | X |  |  |  |  |  |  |  |
| Mother’s Reaction to Pregnancy | X |  |  |  |  |  |  |  |
| Mother’s Family’s Reaction to Pregnancy | X |  |  |  |  |  |  |  |
| Mother’s Health Supplement Use (separate questions for multi-vitamins, folic acid, iron, calcium) Before and During Pregnancy | X |  |  |  |  |  |  |  |
| **Category** | **Measure/Information Obtained** | **BL** | **3** | **6** | **12** | **18** | **24** | **36** | **48** |
|  | Number of Health Visits and Checkups During Pregnancy | X |  |  |  |  |  |  |  |
| Number of Previous Pregnancies (incl. those not to full term) | X |  |  |  |  |  |  |  |
| Maternal Age at Previous Pregnancies (incl. those not to full term) | X |  |  |  |  |  |  |  |
| Mother’s Birth Control Practices | X |  |  | X | X |  | X | X |
| **Parenting/**  **Neglect** | Assessment of Parenting Risks: *Adult-Adolescent Parenting Inventory II (AAPI-II)* | X |  |  | X |  |  |  |  |
| Mother’s Knowledge on Parenting Practices and Child Development Norms: *Knowledge of Infant Development Inventory (KIDI-Short Form)* | X |  |  | X |  |  |  |  |
| Children and Their Parents: *Parental Locus of Control* |  |  | X |  |  |  |  |  |
| Maternal Attachment: *Condon Maternal Attachment Scale* |  |  | X |  |  | X |  |  |
| Feelings about Parenting: *Parenting Stress Index* |  |  | X |  |  | X |  | X |
| Parenting Stress: *Parenting Daily Hassles Scale* |  |  |  |  | X |  | X | X |
| Separation Anxiety: *Maternal Separation Anxiety Scale (General Separation Anxiety Scale only)* |  |  |  |  | X |  |  |  |
| Maternal Perceptions and Behaviours: *Parental Cognitions and Conduct Towards Infant Scale (PACOTIS)* |  |  | X |  |  | X |  |  |
| Parenting Behaviour: *Parenting Styles and Dimensions Questionnaire* |  |  |  |  |  |  | X | X |
| Parental Acceptance: *Parental Acceptance-Rejection Questionnaire* |  |  |  |  |  |  | X |  |
| Child Protective Services Involvement |  |  |  | X |  | X | X | X |
| Parenting Resources |  |  |  | X |  |  | X |  |
| Activities with Baby/Child |  |  | X |  | X |  | X |  |
| Activities with Baby/Child: *Home Learning Environment (HLE)* |  |  |  |  |  |  |  | X |
| Parental Attitudes Toward Education |  |  |  |  |  |  | X |  |
| Parental Monitoring of TV |  |  |  |  |  |  | X | X |
| **Maternal Social Support** | Level of Support Mother receives from Family, Partner, Friends, Neighbours, Work Colleagues, and *PFL* Programme | X |  | X |  | X | X | X | X |
| Mother’s Comfort Level Asking for Help | X |  |  |  |  |  |  |  |
| Mother’s Frequency of Meeting with Friends/Relatives | X |  | X | X |  | X | X | X |
| Mother: Number of Neighbours Know Personally | X |  |  |  |  |  | X |  |
| Mother’s Participation in Organizations | X |  |  |  |  | X |  |  |
| Frequency of Community Services Use (63 services) | X |  | X |  | X |  | X |  |
| Child Contact with/help from Grandparents |  |  | X | X |  |  |  |  |
| Mother Number of Neighbours with Child |  |  | X | X |  | X | X | X |
| Mother Contact with Other People in Programme |  |  | X | X | X |  | X | X |
| Mother Share Programme Information |  |  | X | X | X | X | X | X |
| Influences Parenting Decisions |  |  | X | X | X | X | X | X |
| **Category** | **Measure/Information Obtained** | **BL** | **3** | **6** | **12** | **18** | **24** | **36** | **48** |
| **Maternal Social Support**  ***(continued)*** | Father’s Involvement with Baby/Child |  |  | X | X | X | X | X | X |
| Satisfaction with Father Involvement |  |  | X | X |  | X |  | X |
| Partner’s Involvement with Baby/Child (if different than father) |  |  | X | X | X | X | X | X |
| Satisfaction with Partner’s Involvement (if different than father) |  |  | X | X |  | X |  | X |
| Father Maintenance |  |  |  | X | X | X | X | X |
| Maternal Social Support: *Maternal Social Support Index (adapted)* |  |  |  |  | X |  | X |  |
| **Maternal Socio-Emotional Functioning** | Personality: *Ten-Item Personality Inventory (TIPI)* | X |  |  |  |  |  |  |  |
| Indicator for Postnatal Depression in Previous Pregnancies | X |  |  |  |  |  |  |  |
| Mother’s self-reported DX of Postnatal Depression in past 6 months |  |  | X |  |  |  |  |  |
| Mother’s self-reported Prescription for Postnatal Depression |  |  | X |  |  |  |  |  |
| Maternal Postnatal Depression (6 months): *Edinburgh Postnatal Depression Scale* |  |  | X |  |  |  |  |  |
| Maternal Postnatal Depression (past 7 days): *Edinburgh Postnatal Depression Scale* |  |  | X |  | X | X | X | X |
| Maternal Self-Esteem: *Rosenberg Self-Esteem scale* | X |  |  |  | X | X |  | X |
| Maternal Self-Efficacy: *Pearlin Self-Efficacy scale* | X |  |  | X |  |  |  | X |
| Maternal Attachment Style : *Vulnerable Attachment Style Questionnaire* | X |  |  |  |  |  |  |  |
| Consideration of Future: *Consideration of Future Consequences Scale* | X |  |  |  |  | X |  |  |
| Maternal Psychological Well-Being: *WHO-5 Index* | X |  | X | X |  |  | X | X |
| Time Perspective Taking: *Future Outlook Inventory (FOI)* |  |  |  | X |  |  | X |  |
| Self-Control: *Baumeister Self-Control Measure* |  |  |  |  | X |  |  |  |
| Social Desirability: *Social Desirability Scale-17* |  |  |  |  |  | X |  |  |
| Maternal Antisocial Behaviour |  |  |  |  |  | X |  |  |
| Family Quality of Life: *Beech Center Family Quality of Life Scale* (exclude physical disability subscale) |  |  |  |  |  |  | X |  |
| Romantic Relationship Quality: *Relationship Quality Index* |  |  |  |  |  |  | X |  |
| **Maternal Health** | Mother’s Health as a Child | X |  |  |  |  |  |  |  |
| Mother’s Height & Pre-pregnancy Weight | X |  |  |  |  |  |  |  |
| Mother’s Current Weight |  |  | X | X |  |  |  |  |
| Mother’s General Health Status | X |  |  | X | X | X | X | X |
| Indicator for Mother has Long Term Illness | X |  |  |  |  |  |  |  |
| Existence and Type of Mother’s Physical Medical Conditions | X |  |  |  |  |  |  |  |
| Existence and Type of Mother’s Psychological Health Conditions | X |  |  |  |  |  |  |  |
| Indicator of whether Mother taking Prescribed Medication | X |  |  |  |  |  |  |  |
| Existence and Type of Family Psychological Conditions | X |  |  |  |  |  |  |  |
| Indicator for whether Mother has/ever had Medical Card | X |  |  |  | X |  |  |  |
| Indicator for whether Mother has/ever had GP Visit Card | X |  |  |  | X |  |  |  |
| Indicator for whether Mother has Private Health Insurance | X |  |  |  |  |  |  |  |
| **Category** | **Measure/Information Obtained** | **BL** | **3** | **6** | **12** | **18** | **24** | **36** | **48** |
| **Maternal Health**  ***(continued)*** | Mother’s Diet/Eating Habits | X |  |  | X |  |  |  |  |
| Mother’s Exercise Habits | X |  |  | X |  |  |  |  |
| Mother’s Health Services Use in last 12 months | X |  |  |  | X |  | X |  |
| Maternal Health since Birth of Baby |  |  | X |  |  |  |  |  |
| Maternal Health During Pregnancy |  |  | X |  |  |  |  |  |
| Mother’s Breathing |  |  | X |  |  |  |  |  |
| Mother’s GP Visits |  |  | X | X | X | X | X | X |
| Family Planning |  |  |  | X | X | X | X | X |
| **Maternal Drug/ Alcohol Use** | Mother’s Cigarette Use Before Pregnancy | X |  |  |  |  |  |  |  |
| Mother’s Reasons for Change in Cigarette Use During Pregnancy | X |  |  |  |  |  |  |  |
| Mother’s Alcohol Use Before Pregnancy (quantity & type) | X |  |  |  |  |  |  |  |
| Mother’s Reasons for Change in Alcohol Use During Pregnancy | X |  |  |  |  |  |  |  |
| Mother’s Drug Use Before Pregnancy (quantity & type) | X |  |  |  |  |  |  |  |
| Mother’s Reasons for Change in Drug Use During Pregnancy | X |  |  |  |  |  |  |  |
| Mother’s Drug Use During Pregnancy | X |  | X |  |  |  |  |  |
| Mother’s Change in Cigarette Use During Pregnancy | X |  | X |  |  |  |  |  |
| Mother’s Alcohol Use During Pregnancy | X |  | X |  |  |  |  |  |
| Mother’s Change in Alcohol Use During Pregnancy | X |  | X |  |  |  |  |  |
| Mother’s Drug Use During Pregnancy | X |  | X |  |  |  |  |  |
| Mother’s Change in Drug Use During Pregnancy | X |  | X |  |  |  |  |  |
| Current Cigarette Use |  |  | X | X | X | X | X | X |
| Indicator if Household Members Smoke in same room as Mother/Baby/Child | X |  | X | X |  |  |  |  |
| Mother’s Current Alcohol Use |  |  | X | X | X | X | X | X |
| Mother’s Current Drug Use |  |  | X | X | X | X | X | X |
| **Breastfeeding** | Indicator for Mother Breastfed in Previous Pregnancies | X |  |  |  |  |  |  |  |
| Mother’s Intention to Breastfeed New Baby | X |  |  |  |  |  |  |  |
| Intergenerational Breastfeeding |  |  | X |  |  |  |  |  |
| Current Breastfeeding Practices |  |  | X | X | X | X |  |  |
| **Environment** | Household Material Deprivation Assessment: *EU-SILC Survey* | X |  |  |  | X |  |  |  |
| Indicators of Household Domestic Social/Emotional Risk | X |  |  | X |  | X |  | X |
| Safety: *Injury Prevention Program Framingham Safety Survey* |  |  | X |  | X |  |  | X |
| Home Environment: *Home Observation for Measurement of the Environment (HOME)* + *Supplement to the HOME for Impoverished Families (SHIF)* |  |  | X |  | X |  | X |  |
| Family Environment: *Family Environment Scale (FES)* |  |  |  | X |  |  | X |  |
| Life Circumstances: *Difficult Life Circumstances* |  |  |  |  | X |  | X |  |
| Mother’s Satisfaction with Neighbourhood | X |  |  |  |  |  | X |  |
| **Category** | **Measure/Information Obtained** | **BL** | **3** | **6** | **12** | **18** | **24** | **36** | **48** |
| **Environment**  ***(continued)*** | Neighbourhood Quality: *Neighborhood Quality Evaluation Scale* |  |  |  |  |  |  | X |  |
| Neighbourhood Crime: *Neighborhood Criminal Events Scale* |  |  |  |  |  |  | X |  |
| Family Routines: *Family Routines Inventory* |  |  |  |  |  |  | X |  |
| **Childcare Programmes** | Mother’s Participation in Parenting Programmes or Classes | X |  |  |  |  |  | X |  |
| Mother’s (Intentions for) Childcare Use | X |  | X | X | X | X | X | X |
| Mother’s (Intentions for) Childcare Type | X |  | X | X | X |  | X | X |
| Mother’s (Intentions for) Childcare Timing | X |  | X | X | X |  |  |  |
| Childcare Cost, Satisfaction, etc. |  |  |  | X | X |  | X | X |
| Preschool Planning |  |  |  |  |  |  | X |  |
| Primary School Attendance |  |  |  |  |  |  |  | X |
| Primary School Planning |  |  |  |  |  |  |  | X |
| School Readiness Traits |  |  |  |  |  |  |  | X |
| **Cognitive Assessment** | Maternal Intelligence: *Wechsler Abbreviated Scale of Intelligence (WASI)* |  | X |  |  |  |  |  |  |
| **General Questions** | Voting Behaviour | X |  | X | X | X | X | X | X |
| Breathing Vignettes |  |  | X |  |  |  |  |  |
| Age Related Questions |  |  |  | X | X | X | X | X |
| Relevant Notes About Interview |  |  | X | X | X | X | X | X |
| **Programme Questions** | Client Satisfaction with Programme |  |  | X | X |  | X | X |  |
| Frequency Mentor/IO Meetings |  |  | X | X | X | X | X | X |
| Contamination Questions |  |  | X | X | X | X | X | X |
| **Hopes/**  **Dreams/**  **Strengths/**  **Difficulties** | Mother’s Hopes and Dreams for New Baby | X |  |  |  |  |  |  |  |
| Family Problems that may Affect New Baby (Mother’s View) | X |  |  |  |  |  |  |  |
| Family Strengths and Qualities (Mother’s View) | X |  |  |  |  | X |  | X |
| Thoughts on being a Mam |  |  | X |  |  | X |  | X |
| Important Events Since Last Interview (Mother’s View) |  |  | X |  | X |  | X | X |
| **Sibling Behaviour** | Sibling Behaviour Questions (for 4 year old siblings only): *Newly Designed Instrument* |  |  | X |  | X |  |  |  |

**Child Survey Content**

| **Category** | **Measure/Information Obtained** | **BL** | **3** | **6** | **12** | **18** | **24** | **36** | **48** |
| --- | --- | --- | --- | --- | --- | --- | --- | --- | --- |
| **Child Development** | Difficult Temperament |  |  | X | X |  |  |  |  |
| Temperament: *Temperament and Atypical Behaviour Scale (TABS) Screener* |  |  |  | X |  |  |  |  |
| Child’s Development - Communication: *ASQ* |  |  | X | X | X | X | X | X |
| Child’s Development – Gross Motor: *ASQ* |  |  | X | X | X | X | X | X |
| Child’s Development – Fine Motor: *ASQ* |  |  | X | X | X | X | X | X |
| Child’s Development – Problem Solving: *ASQ* |  |  | X | X | X | X | X | X |
| Child’s Development – Personal-Social: *ASQ* |  |  | X | X | X | X | X | X |
| Child’s Development – Social-Emotional: *ASQ: SE* |  |  | X | X | X | X | X | X |
| Language: *MacArthur-Bates Communicative Development Inventories (CDI)* |  |  |  | X | X | X |  |  |
| Reading/Books |  |  |  | X |  |  |  | X |
| Special Services Child is Receiving |  |  |  | X | X | X | X | X |
| Maternal Developmental Concerns |  |  |  | X |  |  | X | X |
| Social Emotional Development: *Brief Infant Toddler Social and Emotional Assessment (BITSEA)* |  |  |  | X | X | X | X |  |
| Peer Interaction: *Experiences with Other Young Children* (from *ITSEA)* |  |  |  |  |  |  | X |  |
| Peer Interaction: *Peer Problems and Prosocial Behaviour* (from *SDQ)* |  |  |  |  |  |  |  | X |
| Cognitive Development – *Developmental Profile 3 (*Cognitive Section) |  |  |  | X | X | X | X | X |
| Toilet Training: *Toilet Training Q (from Developmental Milestones)* |  |  |  |  |  |  |  | X |
| Child Behaviour *(CBCL)* |  |  |  |  |  | X | X | X |
| Child Development (direct assessment): BAS III Picture Similarities |  |  |  |  |  |  |  | X |
| Child Development (direct assessment): BAS III Naming Vocabulary |  |  |  |  |  |  |  | X |
| Child Development (direct assessment): BAS III Verbal Comprehension |  |  |  |  |  |  |  | X |
| Child Development (direct assessment): BAS III Copying |  |  |  |  |  |  |  | X |
| Child Development (direct assessment): BAS III Matrices |  |  |  |  |  |  |  | X |
| Child Development (direct assessment): BAS III Pattern Construction |  |  |  |  |  |  |  | X |
| Executive Functioning & Delay of Gratification: Gift delay tasks |  |  |  |  |  |  |  | X |
| **Child Health** | Baby’s Birth Weight |  |  | X |  |  |  |  |  |
| Age (in days) When Baby Returned Home from Hospital |  |  | X |  |  |  |  |  |
| Baby’s Health Since Birth |  |  | X |  |  |  |  |  |
| Crying Habits/Patterns |  |  | X |  |  |  |  |  |
| Sleeping Habits/Patterns |  |  | X | X |  |  |  |  |
| Sleep: *Children’s Sleep Habits Questionnaire (CSHQ)* |  |  |  |  |  |  |  | X |
| Medical Visits in Last 6/12 Months |  |  | X | X | X | X | X | X |
| Hospital Inpatient Visits in Last 6/12 Months |  |  | X | X | X | X | X | X |
| Accidents and Injuries Requiring Medical Attention in Last 6/12 Months |  |  | X | X | X | X | X | X |
| **Category** | **Measure/Information Obtained** | **BL** | **3** | **6** | **12** | **18** | **24** | **36** | **48** |
| **Child Health**  ***(continued)*** | Immunizations |  |  | X | X | X |  |  |  |
| Breathing Difficulties |  |  | X |  |  |  |  |  |
| Nutrition/Eating Habits/Patterns |  |  | X | X | X | X | X | X |
| Child’s Current Weight (Mother Report) |  |  | X | X | X | X | X | X |
| Child’s Current Weight (RA Assessed) |  |  |  |  |  | X | X | X |
| Child’s Weight at Last [name] |  |  |  | X | X |  |  |  |
| Child’s Health in Last 6/12 Months |  |  |  | X | X | X | X | X |
| Any Diagnosed Chronic Illness |  |  |  |  |  |  | X | X |
| Any Diagnosed Physical Disability |  |  |  |  |  |  | X | X |
| Child Have Asthma |  |  |  |  |  |  |  | X |

**11. STUDY TREATMENT vigilanceSafety Reporting**

**11.1 Adverse Event (AE)**

An AE is any untoward occurrence which does not necessarily have a causal relationship with the trial treatment. An AE can therefore be any unfavourable and unintended sign, symptom, or disease temporally associated with the trial treatment, whether or not considered related to the treatment.

AEs will be collected from the time of randomisation until the final 48-month follow-up visit for each participant.

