# 1. TRIAL SUMMARY

| **TITLE** | A randomised trial to determine the effectiveness of the Preparing For Life programme which aims to improve the school readiness skills of socioeconomically disadvantaged children in Dublin, Ireland |
| --- | --- |
| **OBJECTIVES** | **Primary objective**  To test the effectiveness of the Preparing for Life (PFL) programme at improving the school readiness skills and life outcomes of socioeconomically disadvantaged children.  **Secondary objective**  To test the effectiveness of the Preparing for Life (PFL) programme at improving parental skills and the quality of the home environment. |
| **DESIGN** | Randomised controlled trial |
| **SAMPLE SIZE** | 300 (100 in randomised high treatment group; 100 in randomised low treatment group and 100 in external comparison group) |
| **STUDY POPULATION** | Pregnant women residing in the PFL catchment area |
| **ELIGIBILITY CRITERIA** | **Inclusion criteria**   1. Women (age 16+) pregnant between 2008 and 2010 2. Residing in the PFL catchment area 3. Willing to be assigned to either of the study intervention groups 4. Written informed parental/carer consent   **Exclusion criteria**   1. Under the age of 16 2. Not pregnant 3. Not residing in the PFL catchment area 4. No written consent provided. |
| **TREATMENT** | **5 year home visiting mentoring programme & group Triple P parenting programme** |

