Investment in early intervention programmes is efficient from both biological and economic perspectives. Intervening early in life, when children are at their most receptive stage of development, has the potential to permanently alter their brain development and subsequent developmental trajectories (Halfon, Shulman, and Hochstein, 2001). Early intervention is also economically efficient. Research on US intervention programmes has demonstrated high rates of return such that the individual and societal benefits accrued from intervening early typically outweigh the costs (Karoly, Kilburn, and Cannon, 2005).

This study describes a randomised control trial (RCT) evaluation of a preventative programme which aims to improve the life outcomes of socioeconomically disadvantaged children. The programme will operate in several disadvantaged communities of Dublin with above national average rates of unemployment, early school leavers, lone parent households and social housing (Census, 2006). The *Preparing for Life* (PFL) programme works with families from pregnancy until school entry in order to promote positive child development through improved parental behaviour and social support.

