**7. Trial Intervention**

**7.1 High treatment intervention**

*PFL* is a community-based home visiting programme (HVP) which aims to improve children’s school readiness skills by intervening during pregnancy and working with families until the children start school at age 4/5 years. The high treatment group will receive twice monthly home visits, lasting approximately one hour, delivered by mentors from a cross-section of professional backgrounds such as psychologists and family support specialists. Mentors will receive extensive training prior to programme implementation and monthly supervision thereafter to ensure fidelity to the programme model. Each family will be assigned the same mentor over the course of the intervention where possible. The mentors will use role modelling, demonstration, coaching, discussion, encouragement, and feedback to deliver the intervention, as well as direct interactions with the child in the presence of the parent. The aim of the visits are to support and educate the parents on key child rearing issues including the identification of developmental milestones and appropriate parenting practices that promote the children’s health, and cognitive and non-cognitive development. Each visit will be guided by a set of *PFL* ‘Tip Sheets’ which are based on pre-existing governmental and local non-governmental organisations’ recommendations, and present best-practice information on pregnancy, parenting, and child health and development. There are three sets of age-specific Tip Sheets - pre-birth-12 months, 1-2 years, and 2-4 years. There are approximately 150 *PFL* Tip Sheets as part of the programme’s curriculum. The mentors will be able to choose when to deliver the Tip Sheets within these specific time periods based on the age of the child and the needs of the family. The Tip Sheets will be given to the participants at the end of each visit to keep as an on-going resource.

The high treatment group will also be invited to participate in an additional parenting course (Triple P Positive Parenting Program; Sanders et al., 2003) when their children are between 2 and 3 years old i.e., after they have completed the 24-month assessment. Triple P promotes healthy parenting practices and positive parent-child attachment. The intervention will involve the delivery of Group Triple P which consists of 5 two-hour group discussion sessions and 3 individual phone calls facilitated by the mentors.

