**11.5 Reporting of SAEs**

Rapid reporting of all SAEs occurring during the study must be performed as detailed in SAE reporting instructions. SAEs will be reported via the eCRF within 24 hours of becoming aware of the event. All reported SAEs will be reviewed by the Chief Investigator (or designee) within 2 working days of receiving notification of the SAE report. The SAE review will be recorded on the eCRF.

SAEs will be followed up until they are resolved.

If the investigator becomes aware of safety information that appears to be related to the treatment, involving a participant who participated in the study, even after an individual participant has completed the study, this should be reported to the Sponsor.

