**16. End of Trial**

The end of the trial will occur when the child of the final participant recruited has completed the last school readiness assessment in the first semester of primary school (~age 4/5 depending on when the child starts primary school).

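### Adverse-event collection stops at the 48-month visit while the programme is described as running to school start, and it is unclear whether that cut-off also limits SAEs

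*Protocol*

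**What the plan says.** Section 11.1 states the collection period for adverse events: "AEs will be collected from the time of randomisation until the final 48-month follow-up visit for each participant".

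Three places describe an intervention that lasts longer. Section 7.1 has mentors "working with families until the children start school at age 4/5 years". Section 2 says that the programme "works with families from pregnancy until school entry". The Trial Summary calls it a "5 year home visiting mentoring programme & group Triple P parenting programme". On frequency, Section 7.1 says "The high treatment group will receive twice monthly home visits" and gives no reduced schedule for later ages.

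The trial itself ends when the last recruited participant's child "has completed the last school readiness assessment in the first semester of primary school" (Section 16).

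Serious events have a separate rule in Section 11.5: "Rapid reporting of all SAEs occurring during the study must be performed as detailed in SAE reporting instructions". That section names no 48-month limit. It also asks for safety information that appears treatment-related to go to the sponsor even after a participant has completed the study. Section 11.4 defines an SAE as an adverse event that meets a seriousness criterion.

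**The concern.** A safety window normally covers at least the period in which the intervention is given. Here the stated window closes at a fixed child age, while the intervention closes at a school event that may come later. Whoever follows Section 11.1 as written stops recording non-serious events while some families are still being visited.

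The second difficulty concerns serious events. Suppose a child has an unexpected hospital admission at 54 months, before starting school. Section 11.5 suggests that it must be reported within 24 hours, because the study is still running. Section 11.1, read with the definition in Section 11.4, could be taken to mean that collection has already closed. Staff could reasonably go either way, and late events might be handled inconsistently.

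Contact with the two randomised groups is also unequal at that point. Table 1 has no family wave after 48 months, and Section 10.4 has teachers complete the school-entry instrument. High-treatment families would still have scheduled mentor visits. Low-treatment families have a support worker to call on if needed (Section 7.2). Late events that come to light only through programme contact would be easier to find in one group than in the other.

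**Working it through.** The protocol states no figure for the gap, so there is none to reproduce. It follows by subtraction.

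**Inputs.** End of adverse-event collection: 48 months of child age (Section 11.1, taking the visit to fall exactly at 48 months). End of intervention: school start at age 4 or 5 (Section 7.1), or 5 years in total (Trial Summary). Scheduled visits: 2 per month in the high treatment group (Section 7.1).

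**Gap by school-entry age.** Gap = age at school start in months − 48.
- Entry at 48 months: 48 − 48 = 0 months.
- Entry at 54 months: 54 − 48 = 6 months.
- Entry at 60 months (fifth birthday): 60 − 48 = 12 months.
- If age 5 is read as any time before the sixth birthday, the last full month is 71: 71 − 48 = 23 months.

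**Cross-check from the stated programme length.** Assume enrolment g months before birth. Five years of programme then end at child age 60 − g, so the gap is 60 − g − 48 = 12 − g.
- g = 1: 11 months.
- g = 7: 5 months.

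The value of g is an assumption. Over the range 1 to 7 the gap is 5 to 11 months, which falls inside the 0 to 12 months obtained from school entry between the fourth and fifth birthdays.

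**Scheduled visits in the gap, per high-treatment family.** Visits = 2 × gap: 6 months gives 12, and 12 months gives 24. These are planned visits, not delivered ones.

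**What is and is not collected after 48 months.**
- Non-serious events: only Section 11.1 governs them, and it closes. They are not collected.
- Serious events, first reading: Section 11.5 stands alone, so SAEs are reportable for as long as the study runs.
- Serious events, second reading: an SAE is an adverse event (Section 11.4), and adverse events are no longer collected (Section 11.1), so routine SAE capture has ended too.
- Treatment-related safety information: reportable at any time under Section 11.5. This does not choose between the two readings, because the SAE rule covers all serious events, whether or not they are related.

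**The case against.** The strongest reply is that nothing important is lost. Section 11.1 can be read as governing routine collection and Section 11.5 as governing serious events, with routine collection ending at 48 months and SAEs reportable to the end. The data monitoring committee reviews SAE reports and key data (Section 17.3), and the annual report to the ethics committee is headed as a report of SAEs (Section 11.9). Both rest mainly on events that Section 11.5 covers. This largely stands. A reader might infer that up to a year of active treatment has no safety coverage at all; the protocol does not support that. For serious events the fault is an ambiguity, not an exclusion.

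A second reply is that little may be delivered after 48 months. Section 7.1 says "There are three sets of age-specific Tip Sheets - pre-birth-12 months, 1-2 years, and 2-4 years", and the last band appears to end at the fourth birthday. That makes the planned content after 48 months unclear. It does not remove the statements in three places that the programme continues to school start or lasts five years.

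A third reply is that 48 months is at least the same child age in both groups, whereas school entry varies by child and could itself respond to a programme aimed at school readiness. This is a fair caution about the choice of a new end point. It does not justify leaving the present mismatch.

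**Conclusion.** The mismatch is real and can be read directly from the text. For children who start school after 48 months, non-serious adverse events go uncollected in the last part of the programme. The gap is 0 months for entry at 48 months and 12 months for entry at the fifth birthday. For SAEs, the protocol does not make clear whether the 48-month cut-off applies.

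The size is not known more closely, because the distribution of entry age is not given. It is tempting to scale up to a trial total: a mean gap of 6 months × 2 visits × 100 families = 1,200 visits. That would require evenly spread entry between ages 4 and 5, no attrition and every visit delivered, none of which the protocol states. It would also measure exposure, not missed events, since no event rate is given.

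The matter is confined to safety reporting. The efficacy analysis, power and error rates are unaffected.

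**What to change.** Reconcile the Trial Summary and Sections 2, 7.1, 11.1, 11.4, 11.5 and 16 on three points.

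1. Align the adverse-event window with the period in which the intervention is delivered. When that delivery ends is for the sponsor to state; the sections need to agree on it.
2. Use the same end definition and the same method of ascertainment in both randomised groups, so that late events do not surface only through mentor visits. If the end is tied to school entry, observation time will vary by child, and event counts should be shown with follow-up time by group.
3. State explicitly that SAE reporting runs to the end of the trial, or state where it stops.

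The cost is a short amendment, slightly more adverse-event recording, and one brief parent contact after 48 months, for example by telephone. That contact has to be added: Table 1 schedules no family wave after 48 months, and teachers complete the school-entry instrument.
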